**1.** **Introduction/Background**

Coronavirus disease 2019 (COVID-19) is caused by the severe acute respiratory syndrome coronavirus 2 (SARS-CoV-2) and has developed into a pandemic with serious global public health and economic sequelae. As of March 30, 2020, over 750,000 cases have been confirmed worldwide leading to over 34,000 deaths (https://coronavirus.jhu.edu/map.html). There is no current vaccine available, but there have been a number of reports of medication such as hydroxychloroquine having antiviral properties with efficacy against SARS-CoV-2.

Plasma therapy using convalescent plasma has been shown to be effective in severe acute respiratory syndrome (1), Ebola virus infection (2) and in H1N1 influenza (3). More recently there has been a report of the use of convalescent plasma in the treatment of 5 ventilated COVID-19 patients with the suggestion of expedited recovery as the patients improved 1 week after the transfusion (4). However, this was not a clinical trial and the patients were on other antiviral medication.; therefore, there is a need to undertake such a trial to see if deploying plasma with SARS-CoV-2 neutralizing antibody has utility in managing patients infected with COVID-19 in respiratory distress.

**2.Objectives**

**Primary objective**

The objective of this pilot study is to compare plasma therapy using convalescent plasma with antibody against SARS-CoV-2 to usual supportive therapy in COVID-19 patients with pneumonia and hypoxia, and to determine if the clinical course is improved. The difference between groups will allow an effect size to be determined for a definitive clinical trial

**Research Question**

**Could** using convalescent plasma transfusion, from recovered COVID19 patients with antibody against COVID-19 be beneficial in treatment of COVID19 patients with hypoxia and pneumonia, in order to avoid or delay the need for invasive ventilation?

**3.Study Design**

This is a prospective, interventional and randomized open label trial involving 40 patients with COVID-19 who are in respiratory distress, with the criteria that all require oxygen therapy and have radiological evidence of pneumonia, 20 of whom will receive a single transfusion of convalescent patient plasma plus routine care, compared to 20 COVID-19 patients who will receive routine care alone.

**Study Arms:**
1. Control group: local standard of care which include antivirals and supportive care
2. Intervention group: convalescent patient plasma plus routine local standard of care

**Outcomes**
Primary outcome is 1) Requirement for invasive ventilation
Secondary outcomes: 1) Time to viral clearance (through the use of CT values) 2) Improvement in biomarkers 3) Radiological Improvement 4) Mortality rate

**Identification of suitable plasma donors among patients recovered from COVID-19**.

Patients who have recovered from COVID-19 and have been discharged from hospital will be approached to see if they will volunteer to be donors

**Criteria for donors**

1. Able to give informed consent
2. Male or nulliparous women(women will need a pregnancy test except for postmenopausal women)
3. At least 14 days after discharge
4. Clinically asymptomatic
5. PCR COVID-19 negative from respiratory tract
6. Patients above the ages of 21 (with no upper age)
7. Body weight more than 50kg
8. At least one week since last glucocorticoid usage.
9. Meet all donor selection criteria employed for routine plasma collection and plasmapheresis procedures at the collection center

Following informed consent, the potential donor will be assessed for suitability to donate blood or plasma through the clinically established donor selection process that includes general health criteria such as such as weight, medical and social (i.e. behavioral risk factors) history, basic physical examination and hemoglobin estimation. One unit of blood will then be taken for transfusion. Donor confidentiality will be maintained throughout and potential donors will be informed that there will be no payment to

them for their plasma donation. A minimum period of 12 weeks will occur in the event of a future blood donation.

Pre-donation testing should include:

1. ABO and RhD grouping,

2. Blood screening tests for HIV, HBV, HCV, syphilis and other locally

transmitted infections, as applicable.

3. Hemoglobin estimation.

4. Nucleic acid testing for SARS-CoV-2.

5. Titration of total COVID-19 antibodies and COVID-19 neutralizing antibodies (If not available, the presence of antibodies qualitatively will be assessed)

6. 3 ml plasma will be retained for viral neutralization experiments.

## Storage of plasma units, inventory management and transportation

- Donated Blood unit will be tested according to the local blood bank protocol.
- Donated Convalescent Plasma will be stored as ‘Plasma Frozen Within 24 hours’ and stored for up to 12 months at or below -18^0^ C in a separate controlled plasma freezer dedicated to the trial. Longer storage period might be considered for research purposes only.
- Both whole blood units and plasma units will be tagged as COVID-19 Donor using labels, separate codes and serial numbers to make them identifiable from others. The plasma container will be labelled as Caution: New Drug Limited by law to investigational use”.
- Sample from convalescent plasma will be stored for determining antibody titer at a later date once validated SARS-CoV-2 neutralizing antibody titer test is available.
- Plasma unit will be transported to COVID center in a special labelled refrigerator and will be arranged between hospitals blood banks.

**Selection of COVID-19 patients**

1. Able to give informed consent

2. COVID-19 patients who have tested positive for SARS-CoV-2, and who are hypoxic and requiring oxygen therapy (Oxygen saturation of less than or equal 92% or PO2 < 60mmHg on ABG)

3. Radiological evidence of pneumonia (any infiltration on CXR or CT scan.)

**Contraindications:**

1. History of allergy to plasma, sodium citrate or methylene blue.

2. History of autoimmune disease or selective IGA deficiency.

**Side effects**

The major potential side effect will be that of a transfusion reaction that may be manifest with increased fever, hypotension and skin rash. This will be minimized by the ABO and RhD grouping that will be taken for each patient.

**Convalescent plasma administration**

ABO and RhD matched plasma units will be selected for transfusion and transfused to the COVID-19 patients using standard clinical transfusion procedures.

The dosage of convalescent plasma will be 400 mL, given as 200ml over 2hrs in 2 consecutive days.

**Study Schedule**

**1: Patient characteristics**

- Patient confirmed to be SARS-CoV-2positive by PCR
- Patients able to give informed consent
- Patients who are hypoxic and requiring oxygen therapy
- Consent, inclusion and exclusion criteria. Patients will be assessed for the inclusion and exclusion criteria of the study by the consultant and consented by a doctor on the clinical team.
- Patient identifiers, admission date, age and sex
- Patient characteristics (yes/no): current smoking, diabetes, heart disease, chronic lung disease, chronic liver disease, chronic kidney disease, asthma, HIV, tuberculosis
- COVID-19 oxygen therapy being given, oxygen saturation on room air, oxygen flow.
- Anthropometric measurement –BMI, blood pressure, temperature, respiratory rate
- ECG
- Baseline bloods: Biochemical profile (BCP), full blood count (FBC), CRP, PCT, LDH, Troponin, Ferritin, D-Dimer, BNP, lactate
- Baseline ABG on room air, on enrolment
- Baseline PaO2 value
- Chest Xray prior to starting plasma transfusion
- ABO and RhD blood grouping and cross-matching
- Baseline SARS-CoV-2 Swab PCR with CT Value (indirect assessment of viral load) through Nasopharyngeal swab.
- Randomization into one of the 2 groups

**2: Daily recording in case report form for 10 days or until discharge**

- blood pressure, temperature, respiratory rate
- Oxygen flow rate and oxygen device for oxygen saturation
- Full blood count(Hb, WBC, Neutrophil count, Neutrophil percent (%),Lymphocyte count, Lymphocyte percent (%),Platelets) , Biochemical profile(Na, K, Urea, Creatinine, LDH), Liver function tests(ALT,AST,ALP,GGT), CRP, PCT, LDH, Troponin, Ferritin, D-Dimer, BNP, lactate
- Date of plasma infusion
- Amount of plasma infusion
- Adverse Event or Adverse Reaction
- Patient’s current medications
- Date of Intubation
- Ventilator Setting if on ventilator

**3: Intermittent recording in case report form for 10 day or until discharge**

- Chest Xray 1 day after completion of plasma therapy or standard treatment and on Discharge
- ABG and PaO2 values after completion of plasma therapy or standard treatment on day 1,2,3 and then every 3 days and on discharge
- SARS-CoV-2 Swab PCR with CT Value , day 1 and 3 after plasma transfusion or standard treatment, every 7 days, and on discharge

*Criteria for discontinuation of the study*.

The study will be discontinued based on any adverse reactions such as transfusion reactions or may be withdrawn by the Ministry of Health decision on safety, or if any superior drug/intervention has been identified and is available

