The following information will be reported: Study name; patient identification, including subject number, initials, sex, age; event (preferably diagnosis); trial drug Reporter Causality Outcome

Determination of causality of an adverse reaction

Probable - Good reason and sufficient documentation to assume a causal relationship.

Possible - A causal relationship is conceivable and cannot be dismissed.

Unlikely - The event is most likely related to aetiology other than the trial product.

Adverse Event reporting period

The AE reporting period for this trial begins as soon as patients have consented to the trial and ends 30 days after the patient’s final study medication visit.

The health status of subjects will be checked at each study visit. The investigator will record all directly observed AEs and all AEs spontaneously reported by the trial subject.

A pre-existing condition is a disorder present prior to the patient entering the trial and does not need to be reported as an AE unless the condition worsens, or episodes increase in frequency during the AE-reporting period. A pre-existing condition will be documented at the screening or baseline study visit.

All adverse events (serious and non-serious) will be recorded by the investigator in patients data collection forms (CRFs) using R&D’s adverse event report form. All adverse events will be recorded by the investigator in patients’ medical records/notes.

All AEs will be followed-up by investigators until the event has resolved or a decision has been taken for no further follow-up.

If a clinically significant abnormal laboratory value occurs, this abnormality will be recorded as an adverse event/reaction.

Reporting serious adverse events

Investigators will notify the sponsor of serious adverse events within 24hrs of becoming aware of the event, together with the REC.

The sponsor will report fatal or life-threatening SUSARs within 5 days and follow-up information within a further 8 days. The investigator will report fatal or life-threatening SUSARs to the IRB within 5 days and follow-up information within a further 8 days by following the request on the Serious Event Initial and Follow-up report forms. The investigator will send all other SUSAR reports to the IRB within a maximum of 15 days.

End of Trial:

The end of the trial will be the date of the last study point of the last patient undergoing the trial.

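### The X-ray, blood-gas and swab schedule counts days from an event that is undefined for the control arm, so nothing ensures that both arms are assessed at the same time since randomisation

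*Protocol*

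**What the plan says.** All of this is in the Protocol.

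- **Chest X-ray** (Study Schedule, part 3): "Chest Xray 1 day after completion of plasma therapy or standard treatment and on Discharge".
- **Blood gases** (same list): "ABG and PaO2 values after completion of plasma therapy or standard treatment on day 1,2,3 and then every 3 days and on discharge".
- **Swabs with CT value** (same list): "day 1 and 3 after plasma transfusion or standard treatment, every 7 days, and on discharge". This line does not mention completion.
- **Recording window** (heading of that list): "Intermittent recording in case report form for 10 day or until discharge". No day 0 is given.
- **Control treatment** (Study Arms): "Control group: local standard of care which include antivirals and supportive care". No start, course length or end is stated. The intervention arm receives the same routine care with plasma added.
- **Plasma** (Convalescent plasma administration): "given as 200ml over 2hrs in 2 consecutive days". The Study Design section instead says "20 of whom will receive a single transfusion of convalescent patient plasma plus routine care".
- **Adverse events** (section 11): "The AE reporting period for this trial begins as soon as patients have consented to the trial and ends 30 days after". Those 30 days are counted from the last visit for study medication.

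The Patient population paragraph places treatment after randomisation but fixes no interval between the two.

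**The concern.** In a randomised comparison both arms should be measured at the same times from a common origin. Here the plasma arm's clock for X-ray, blood gases and swabs starts at an event that only that arm has. The control arm's clock starts at an event that is never dated. Standard treatment cannot serve as the control counterpart of plasma, because it has no defined end and both arms receive it.

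CT values, infiltrates and blood gases change over the course of the illness whatever is given. If one arm is measured earlier or later than the other, a difference can appear without any treatment effect, or a real one can be hidden. Two of the four secondary outcomes, time to viral clearance and radiological improvement, rest on these assessments. The stated purpose of the pilot is to supply an effect size for a definitive trial, so an artefact would carry into that trial's planning. An analysis plan cannot repair this later, because tests not taken at comparable times are lost.

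**Working it through.** The plan states no figure that depends on this schedule, so there is nothing to reproduce. The check is calendar arithmetic, followed by two illustrations.

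**1. Calendar, in days since randomisation (day 0).** Let w be the day of the first transfusion and L the day on which a control patient's standard treatment counts as completed. The protocol gives neither, so both are assumptions.

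- Plasma over two days: the last transfusion is on day w+1, the X-ray on w+2, and the swabs on w+2 and w+4 if counted from completion. For w = 0, 1, 2, 3 the X-ray falls on day 2, 3, 4, 5.
- Plasma as one transfusion: the X-ray falls on day w+1, one day earlier. The conflict between the two descriptions of plasma therefore moves this arm's anchor by a day.
- Control: the X-ray is on day L+1 and the swabs on L+1 and L+3. For L = 0, 5, 7, 10 the X-ray falls on day 1, 6, 8, 11. At L = 10 it is outside a 10-day window counted from randomisation.

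The arms coincide only if L = w+1 (two transfusion days) or L = w (one). Nothing in the protocol requires either.

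**2. Viral clearance with no treatment effect.** Assume that true clearance times are exponential with the same median m in both arms, so the share cleared by day t is 1 − 2^(−t/m). Take w = 1, which puts the first plasma-arm swab on day 3.

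| Assumed median m | Plasma, day 3 | Control L = 0, day 1 | Control L = 5, day 6 | Control L = 7, day 8 |
|---|---|---|---|---|
| 5 days | 34% | 13% | 57% | 67% |
| 7 days | 26% | 9% | 45% | 55% |
| 10 days | 19% | 7% | 34% | 43% |

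Plasma looks better if controls are swabbed on day 1 and worse if they are swabbed on day 6 or 8, although the arms are identical.

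The median day of the first observed negative moves too. It is the first swab day on or after m. Reading the weekly swabs as following the day-3 swab, the plasma grid is days 3, 5, 12, 19.

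- For m = 7 the median is day 12 (plasma) against day 10 (L = 0), day 8 (L = 5) and day 8 (L = 7).
- For m = 10 it is day 12 (plasma) against day 15 (L = 5; grid 6, 8, 15), so the order reverses.

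Cases where a swab day falls exactly on m are left out, because the observed median is then not stable. These medians also let swabs continue past day 10 and ignore the discharge swab, so the first-swab shares in the table are the firmer illustration.

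**3. Continuous measures.** Suppose the timing difference shifts one arm's mean by δ SD, with 20 per arm and a two-sided 5% t test on 38 degrees of freedom (critical value 2.024). The noncentrality is δ / √(2/20) = δ / 0.316.

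| δ (SD) | Noncentrality | Rejection rate with no treatment effect |
|---|---|---|
| 0.1 | 0.316 | 6.1% |
| 0.2 | 0.632 | 9.5% |
| 0.3 | 0.949 | 15.2% |
| 0.4 | 1.265 | 23.4% |

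These δ correspond to an offset of 1 to 2 days and a natural drift of 0.1 to 0.2 SD per day: 1 × 0.1 = 0.1 at the low end, 2 × 0.2 = 0.4 at the high end. Both ranges are assumptions.

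**The case against.** The strongest reply is that this touches little of what the trial is for. It is a self-described pilot. The primary outcome is invasive ventilation, and the date of intubation is recorded daily in both arms. Mortality does not use the anchor. The biomarkers are also recorded daily, and the discharge X-ray, blood gas and swab are tied to discharge. All of this stands and limits the point to the assessments in part 3 of the schedule.

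A second reply is that sites would in practice count controls from randomisation. The text does not say so. If they did (L = 0), controls would have their X-ray on day 1 and plasma patients on day w+2, so the arms would still differ under the two-day description. Reading the swab line as counting from the start of treatment does not help either, because the start of standard treatment is not dated.

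A reader might infer more than the document supports:

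- *That the arms certainly are measured at different times, or that the error favours plasma.* Neither the wait for plasma nor the control anchor is given, so size and direction are unknown.
- *That standard care as a whole began before enrolment.* The entry criteria and baseline record show this for oxygen only. No start is stated for antivirals.
- *That time to clearance suffers immortal-time bias.* That needs a clock starting at transfusion. The Statistical Analysis section names time-to-event and intention-to-treat analysis without such an origin, and an analysis plan commonly fixes the origin.
- *That the rejection rates estimate the trial's true error rate.* They rest wholly on assumed inputs. At 0.1 SD the rate is close to nominal, and the t-test model does not describe a time-to-event outcome.

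**Conclusion.** The point holds as a defect in the schedule. The control-arm anchor is undefined, and nothing in the protocol ties the post-baseline X-ray, blood gases and pre-discharge swabs to randomisation, so equal timing would be a coincidence. It can distort time to viral clearance, radiological improvement and blood gases in either direction. The primary outcome, mortality, daily biomarkers and discharge assessments are not affected.

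The size cannot be derived from the document. The 6% to 23% rejection rates depend on an assumed artefact of 0.1 to 0.4 SD. The first-swab shares depend on an assumed clearance curve and assumed values of w and L.

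There is a secondary point of the same kind. The adverse-event window ends relative to a study-medication visit, which has no clear meaning for patients who receive no study plasma.

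This should be fixed. It does not put the primary comparison at risk.

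**What to change.** - **Common day 0.** Define day 0 as randomisation in both arms. Schedule the X-ray, blood gases and swabs on the same fixed days from randomisation in both arms, with the first after the planned plasma period. Keep the date of plasma as a recorded variable, as the daily record already provides.
- **Plasma description.** Reconcile the single transfusion in the Study Design section with the two consecutive days in the administration section, since the plasma completion date depends on it. Which is intended is for the sponsor to state.
- **Adverse-event window.** State an end point that applies to both arms without shortening the plasma arm's follow-up. Simply ending it 30 days after randomisation would cut post-plasma follow-up by however long plasma takes to be given.

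**Cost.** Part 3 of the Study Schedule and the adverse-event reporting period need rewording, with about the same number of tests. Time since transfusion will vary within the plasma arm, and an early assessment may precede plasma completion if plasma is delayed. The protocol sets no limit on that wait, so the variation cannot be bounded from the document.

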**11.Provisions to Monitor the Data to Ensure the Safety of Subjects**

Safety considerations/Patient safety:

Safety monitoring will be undertaken as a part of the clinical trial. A data safety monitoring board will be convened to review safety data on a weekly basis during the conduct of the study.

The major potential side effect will be that of a transfusion reaction that may be manifest with increased fever, hypotension and skin rash. This will be minimized by the ABO and RhD grouping that will be taken for each patient.

An interim review and report to the clinical trial committee will be undertaken when 20 subjects have been recruited

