**Definitions**

| **Term** | **Definition** |
| --- | --- |
| **Adverse Event (AE)** | Any untoward medical occurrence in a participant to whom a medicinal product has been administered, including occurrences which are not necessarily caused by or related to that product. |
| **Adverse Reaction (AR)** | An untoward and unintended response in a participant to an investigational medicinal product which is related to any dose administered to that participant.  The phrase "response to an investigational medicinal product" means that a causal relationship between a trial medication and an AE is at least a reasonable possibility, i.e. the relationship cannot be ruled out.  All cases judged by either the reporting medically qualified professional or the Sponsor as having a reasonable suspected causal relationship to the trial medication qualify as adverse reactions. |
| **Serious Adverse Event (SAE)** | A serious adverse event is any untoward medical occurrence that:   - results in death - is life-threatening - requires inpatient hospitalisation or prolongation of existing hospitalisation - results in persistent or significant disability/incapacity - consists of a congenital anomaly or birth defect   Other ‘important medical events’ may also be considered serious if they jeopardise the participant or require an intervention to prevent one of the above consequences.  NOTE: The term "life-threatening" in the definition of "serious" refers to an event in which the participant was at risk of death at the time of the event; it does not refer to an event which hypothetically might have caused death if it were more severe. |
| **Serious Adverse Reaction (SAR)** | An adverse event that is both serious and, in the opinion of the reporting Investigator, believed with reasonable probability to be due to one of the trial treatments, based on the information provided. |
| **Suspected Unexpected Serious Adverse Reaction (SUSAR)** | A serious adverse reaction, the nature and severity of which is not consistent with the information about the medicinal product in question set out:   - in the case of a product with a marketing authorisation, in the summary of product characteristics (SmPC) for that product - in the case of any other investigational medicinal product, in the investigator’s brochure (IB) relating to the trial in question |

Reporting adverse events

Adverse events will be reported in accordance with the local procedures to the REC of NHRA

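### The study-level safety stop is set at any adverse reaction, with no seriousness threshold and no link to the safety board

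*Protocol*

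**What the plan says.** The stopping criterion stands in Protocol section 3, at the end of the Study Schedule, under the heading on criteria for discontinuing the study: "The study will be discontinued based on any adverse reactions such as transfusion reactions". The same sentence goes on to two other grounds, a Ministry of Health decision on safety and the arrival of a superior intervention. The verb for the Ministry ground is permissive (may), whereas the verb for reactions is not (will).

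The Definitions table in section 11 describes an adverse reaction as "An untoward and unintended response in a participant to an investigational medicinal product which is related to any dose administered to that participant". It counts an event as related when "a causal relationship between a trial medication and an AE is at least a reasonable possibility". Severity plays no part. A serious adverse reaction is a separate entry: "An adverse event that is both serious and, in the opinion of the reporting Investigator, believed with reasonable probability".

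Under Side effects, and again in section 11, the foreseen harm is named: "The major potential side effect will be that of a transfusion reaction that may be manifest with increased fever, hypotension and skin rash".

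On oversight, section 11 says: "A data safety monitoring board will be convened to review safety data on a weekly basis during the conduct of the study". It adds: "An interim review and report to the clinical trial committee will be undertaken when 20 subjects have been recruited". Neither sentence gives a stopping threshold, and the stopping criterion in section 3 refers to neither.

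**The concern.** The criterion uses the broadest safety term that the protocol defines, although a narrower one is available in its own table. A mild rash or a rise in temperature after plasma, possibly due to it, is an adverse reaction under that table. It is also the kind of event the protocol expects. If staff apply the sentence as it stands, the first such event closes the study.

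The stated purpose of the pilot is to supply an effect size for a definitive trial (section 2, and section 9 on sample size). An early stop leaves fewer patients for that estimate. The clause also gives the weekly board no role in the decision, so staff who see a first mild reaction cannot tell from the protocol whether to halt the study or report the event and carry on.

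**Working it through.** **Text.** Four features favour the literal reading:

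- The heading refers to the study, not the patient.
- The reaction clause says will, where the Ministry clause says may.
- Adverse reaction is a defined term with no severity requirement, and the separately defined serious reaction is not used.
- The example given, a transfusion reaction, is the main foreseen side effect.

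No threshold elsewhere in the protocol qualifies the clause.

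**Inputs.** There are 20 plasma patients (sections 3 and 9). The protocol states no reaction rate and no operating characteristic for the rule, so there is no figure to reproduce. I assume a per-patient reaction probability r of 1%, 3%, 5% or 10%, independence between patients, a stop that takes effect at the first patient with a reaction, and equal arms at that moment. All results below apply to the literal reading only.

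**Formulas.**

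- Chance of at least one reaction in 20 plasma patients: 1 − (1 − r)^20.
- Chance of a reaction in the first 10 plasma patients, roughly the number treated by the interim review at 20 recruited: 1 − (1 − r)^10.
- Expected plasma patients treated, m: the sum of (1 − r)^k for k = 0 to 19, which is [1 − (1 − r)^20] / r.
- Relative width of the confidence interval for the risk difference at m per group instead of 20: √(20/m), taking the same ventilation risks.

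For r = 3%: 0.97^20 = 0.544, so the first chance is 0.456; m = 0.456/0.03 = 15.2; relative width = √(20/15.2) = 1.15.

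| Assumed r | At least one in 20 | At least one in first 10 | Expected treated, m | Relative interval width |
|---|---|---|---|---|
| 1% | 18.2% | 9.6% | 18.2 | 1.05 |
| 3% | 45.6% | 26.3% | 15.2 | 1.15 |
| 5% | 64.2% | 40.1% | 12.8 | 1.25 |
| 10% | 87.8% | 65.1% | 8.8 | 1.51 |

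The width column is evaluated at the expected size; a single study could stop earlier or later. If the same rates applied per infusion (two per patient, so 40 infusions), the chance of at least one reaction would be 33%, 70%, 87% and 98.5%.

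**Against section 9.** The stated minimum there is 20 degrees of freedom. A pooled two-group comparison has 2m − 2, which is about 34, 28, 24 and 16 at the expected sizes. Only the 10% rate brings the expected size below 20. The minimum is reached at 11 per group (2 × 11 − 2 = 20). The chance of a reaction before the 11th plasma patient is treated is the first-10 column.

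**After the change proposed below.** If serious adverse reactions occur at an assumed 0.5%, 1% or 2% per patient, the chance of at least one urgent referral to the board in 20 plasma patients is 9.5%, 18.2% or 33.2%. A referral does not in itself stop the study.

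**The case against.** The strongest reply is that no automatic stop was meant. The words based on can name a ground that someone weighs. Much of the protocol fits a study that continues after reactions: daily recording of "Adverse Event or Adverse Reaction", weekly board review, follow-up of events until they resolve, up to 15 days for SUSAR reports that are neither fatal nor life-threatening, and 5 days for non-serious events. The clause also follows directly on per-patient schedules and may be loosely worded. This stands in part: intent is uncertain, and a reader who infers that the sponsor certainly planned to stop at the first mild reaction goes beyond the text. It does not remove the problem, because on the softer reading the clause still gives no threshold and names nobody to decide.

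A low tolerance for harm from an unproven blood product is a legitimate choice, and operational thresholds may sit in a board charter that is not at hand. But the protocol does not present the clause as such a choice and does not refer to a charter.

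Three stronger inferences are tempting and fail:

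- **That the rule cannot be followed.** It can; the literal rule is clear and very cautious.
- **That the interval would be about 1.41 times as wide.** That is √(20/10), which supposes a stop at exactly 10 per group. At the expected sizes the factor is below that for three of the four assumed rates.
- **That any stop short of 20 per group fails the pilot's own requirement.** Section 9 sets its minimum in degrees of freedom, and a pooled comparison meets it from 11 per group.

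**Conclusion.** The point holds as a badly fixed criterion. The protocol sets the study-level stop at any adverse reaction, without a seriousness threshold or a link to its own safety board, and a literal reading ends the pilot at the first mild, foreseen reaction.

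The size of the consequence rests wholly on assumed reaction rates. Across 1% to 10% per patient, the chance that the literal rule is triggered runs from 18% to 88%, and the loss of precision at the expected size runs from slight (1.05) to substantial (1.51). At 1% no reaction would occur in 82% of such studies, so the rule would usually not fire.

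The harm is lost precision for the effect-size estimate. A reader might infer bias as well, but nothing in the documents supports that. If only a ground for stopping was meant, what remains is an ambiguous instruction, which the same amendment settles.

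**What to change.** Replace only the adverse-reaction clause of the discontinuation criteria with:

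> Any serious adverse reaction is referred at once to the data safety monitoring board, which recommends whether the study continues, pauses or stops; non-serious reactions go to its weekly review.

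Keep the Ministry of Health and superior-intervention grounds. Nothing need be added on stopping an individual infusion or on keeping the patient in the intention-to-treat analysis: the section on plasma administration leaves infusions to standard transfusion procedures, and sections 6 and 10 already provide for intention-to-treat analysis.

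The cost is a one-sentence amendment. It uses the definition of a serious adverse reaction, the 24-hour notice of serious events and the weekly board, all of which section 11 already has, and needs no extra patients or staff. The small downside is that the study no longer stops automatically at the first reaction; the board's judgement takes the place of that stop.
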